## **11 Trial Risk Category, Potential benefits and risks for participating patients.**

This trial is categorised (based on MRC/DH/MHRA joint project 10th October: Risk-adapted Approaches to the Management of Clinical Trials of Investigational Medicinal Products) as:

- Type B = Somewhat higher than the risk of standard medical care

Justification: Ulipristal acetate (UA) 5mg is an established licensed drug in the UK for use in the treatment of uterine fibroids. UA will be used in a new indication in this trial for breast cancer prevention and has therefore been categorised as type B.

### **11.1 Benefits:**

It is unlikely that any physical benefits will result from participation in this trial. Even if the hypothesis that antiprogesterin therapy may reduce BC risk is correct, any risk reduction with only 3 months of therapy is likely to be negligible.

### **11.2 Risks:**

The gadolinium contrast agent given during the MRI scans can cause mild nausea and rarely headache and/or vomiting. Allergic reactions are rare (~1 in 10,000) and generally respond well to standard treatment. All contrast agent injections will be supervised by a medical practitioner.

By participating in this study women will have at least one and some will have 2 vacuum assisted biopsies of the breast(s). The risks associated with VABs including pain, bruising, haematoma, bleeding, infection and scarring of the breast are detailed in the patient information sheet. To mitigate against these risks only experienced radiologists will perform study VABs [name]. Additional physical harms come from the blood tests that would otherwise not be performed.

Should pregnancy occur in any of the trial participants, the risk to the foetus is unknown. However UA is known to induce anovulation and therefore pregnancy is less likely than without the use of the drug.

### **Risks mitigations:**

The MRI unit performing the scans have medical cover and medication available on site should a contrast reaction occur. Participants who have an eGFR <60 ml/min/1.73m^2 will be excluded. A serum pregnancy test will be carried out at screening. Urine pregnancy tests will then be carried out at each 4 week visit through the trial and the importance of using contraception will be emphasised at multiple points throughout the trial. To prevent recruitment of women with breast cancer a sample of the baseline VAB biopsy will be

examined by an accredited breast pathologist before trial eligibility is confirmed.

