#### 4. Trial Summary

A summary of trial procedures is provided in Appendix 4.

30 premenopausal women at moderate to high risk of BC (NICE guidelines) will be recruited from family history clinics in a similar manner to previous successful biopsy and dietary intervention studies (Ong 2009; Evans 2010), using mailshot and clinic visit recruitment. Subjects will be confirmed to be in an ovulatory menstrual cycle prior to performance of baseline breast MRI scan and vacuum assisted biopsy (VAB) of the most dense region of one breast. Ideally 10 cores of breast tissue will be taken. After the onset of the next menstrual cycle subjects will start UA 5mg daily and be reviewed every 4 weeks in trial clinics for blood tests and toxicity assessment. In the 12th week of therapy subjects will have a repeat breast MRI scan followed by either VAB of the contralateral breast or prophylactic mastectomy with harvest of breast tissue (from the predetermined contralateral isodense region from baseline MRI). UA will then be discontinued and one further safety visit planned for 4 weeks post completion (figure 2).

Once the participant has had their visit 4 appointment they will be sent an invite to provide a saliva sample for the purpose of DNA analysis. Should they wish to participate in this part of the study a telephone appointment will be made for them. At this appointment a study doctor will discuss the analysis which will be undertaken. Following the discussion, if the participant is happy to proceed, they will be sent a consent form to complete and return to research team.

Once the consent form has been received by the study team, a helix tube for saliva collection will be posted to the participant. The participant will be provided with a return envelope to post the sample to the genetics team at St Mary's Hospital, Manchester.

When the results of the DNA analysis are available an appointment will be made for the participant to be reviewed either as a telephone appointment or to attend the Nightingale Centre for feedback with a study doctor.

Figure 2: Trial schema

[figure not shown]

The end of the trial will be when the last participant has received their DNA analysis results – no further data will be collected after this point.

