### 6.1. Inclusion Criteria

- Premenopausal females aged between 25 and 45 years
- Regular menses defined as date of onset of last menstrual period +/- 3 days of expected
- Willing to use an acceptable method of contraception from screening to 2 weeks after study drug discontinuation (see Restrictions section 5.3 below)
- Known BRCA1 or BRCA2 mutation or moderate to high risk of developing BC defined as >17% lifetime risk from age 20 or >3% risk between 40-50 years
- Ovulatory menstrual cycles defined as serum progesterone  $\geq 15\text{nmol}$  in the luteal phase of the menstrual cycle (2 weeks prior to expected onset of menses).

- Willing and able to provide informed consent to undergo all trial procedures.

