**Visit 4 Day 113  $\pm$  4 days (week 17)**

During this visit the participant will:

- be asked if they are happy to continue in the trial
- have adverse events from the VAB visit and any other adverse events documented
- have any changes in their concomitant medications documented
- have their weight recorded
- have blood samples taken for LFT of which bilirubin, ALT, ALP, LDH will be measured
- be asked if they have started their menstrual period

Should a participant experience treatment emergent clinical symptoms or signs of liver disease whilst participating in the study they will be advised to contact the research team as soon as possible for assessment which will include repeat LFTs of which bilirubin, ALT, ALP and LDH will be recorded. Therefore, assessments of this nature could be conducted outside of the scheduled study visits.

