### **13.4 The type and duration of the follow-up of subjects after adverse events.**

Adverse events will be followed up until the safety visit 4 weeks after the last dose of IMP.

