| Urine pregnancy test                                                                                 |                                |                                                |                                                                                                | X                                     | X                                  | X                             |                                          |                                                                                                                                                                                                                                                      |
| Dispense ulipristal acetate 5mg daily: 3 x 28 day packs                                              |                                | X                                              |                                                                                                |                                       |                                    |                               |                                          |                                                                                                                                                                                                                                                      |
| Patient to start supply of dispensed UA                                                              |                                |                                                | X                                                                                              |                                       |                                    |                               |                                          |                                                                                                                                                                                                                                                      |

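### No pregnancy test is scheduled after ulipristal exposure ends: Section 11.2 promises urine tests at each 4-week visit, but Section 7.1 and Appendix 5 stop at Day 78-85

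*Protocol*

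**What the plan says.** The risk mitigations under Section 11.2 provide a serum pregnancy test at screening, and then: "Urine pregnancy tests will then be carried out at each 4 week visit through the trial". The same section explains the need: "Should pregnancy occur in any of the trial participants, the risk to the foetus is unknown".

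The operational schedule is in Section 7.1 and Appendix 5:

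| Visit | Day | Pregnancy test (Section 7.1) | Appendix 5 |
|---|---|---|---|
| Screening | 7 days before expected menses, ± 4 | serum | marked (serum row) |
| Visit 1 | 29 (+4/−7) | urine | marked |
| Visit 2 | 57 (+4/−7) | urine | marked |
| Visit 3 | 78-85 | urine | marked |
| Visit 4 | 113 ± 4 | none | blank |

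The Appendix 5 row headed "Urine pregnancy test" is therefore empty in the week 17 column. The nearest item in the Visit 4 list is that the woman will "be asked if they have started their menstrual period". The list states no action to follow from her answer.

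Section 4 says that women on UA will "be reviewed every 4 weeks in trial clinics for blood tests and toxicity assessment", and then describes Visit 4 as "one further safety visit planned for 4 weeks post completion". Section 13.4 closes safety follow-up at that visit: "Adverse events will be followed up until the safety visit 4 weeks after the last dose of IMP". Under Section 6.1 a participant must be: "Willing to use an acceptable method of contraception from screening to 2 weeks after study drug discontinuation".

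**The concern.** The mitigation text promises testing throughout the trial at 4-week visits, and Visit 4 looks like one of them: nominal Days 29, 57, 85 and 113 are each 28 days apart. Yet Visit 4 has no test.

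The practical problem does not depend on the wording. The Visit 3 test is done at or just before the last dose, so it cannot show a conception from the last part of the treatment period. After it, the plan relies on the woman reporting a pregnancy, or on staff choosing to act on the menses answer. That answer is a weak signal, because Section 5.6.3 describes delayed or absent menstruation as an expected effect of UA, so a missing period soon after stopping could be attributed to the drug.

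The adverse event enquiry at Visit 4 need not capture pregnancy either. Section 13.7 does not count pregnancy as an adverse event unless there is a negative or consequential outcome. It requires a report within 24 hours of learning of a pregnancy but gives no means of learning of one. The only contacts after Visit 4 are the optional DNA appointments.

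What is at stake is finding exposed pregnancies and following their outcome. A Visit 4 test would not reduce exposure, and the Ki67 and other efficacy analyses are untouched.

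**Working it through.** The plan gives no figure on this point to reproduce. The check is the comparison of schedules shown above, plus day arithmetic.

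**Inputs from the protocol**
- Visit 3 and the second biopsy (or mastectomy) share the Day 78-85 window, and UA stops after the biopsy or mastectomy (Sections 4 and 7.1).
- Visit 4 is on Day 113 ± 4, i.e. Day 109-117 (Section 7.1).
- 30 women (Section 4).
- UA induces anovulation in 70-80% of women (Section 5.4.1), so 20-30% may still ovulate.

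**Assumptions, not in the protocol**
- Lag from conception to a positive urine test: 10-18 days.
- Contraceptive failure in ovulating women: 1-20% per year.

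**Exposed time that no test covers, per woman**
- Before the Visit 3 test, conceptions too recent to detect: 10 to 18 days.
- From the Visit 3 test to the last dose: 0 to 85 − 78 = 7 days.
- Total: 10 + 0 = 10 days to 18 + 7 = 25 days.
- In 30 women: 30 × 10 = 300 to 30 × 25 = 750 woman-days.

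**Expected pregnancies in that time**

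Formula: women × (days / 365) × annual failure × share ovulating.
- Low: 30 × (10/365) × 0.01 × 0.20 = 0.0016.
- High: 30 × (25/365) × 0.20 × 0.30 = 0.123.

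**Would a Visit 4 test cover the gap?**
- Shortest interval from last dose to Visit 4: 109 − 85 = 24 days.
- Longest: 117 − 78 = 39 days.
- Both exceed the longest assumed lag of 18 days, so even a conception on the day of the last dose would be detectable. One test covers the whole window.

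**The case against.** The strongest reply is that the protocol does not contradict itself. Section 4 uses the 4-weekly phrase for reviews on UA and then names Visit 4 separately as a further safety visit. Read that way, the mitigation text, Section 7.1 and Appendix 5 agree, and what remains is a preference for one more test. The protocol already has a serum test at screening, three urine tests, repeated contraception counselling, exclusion of women planning pregnancy within 6 months, and the menses question. Section 13.7 gives pregnancy its own monitoring rule, so Section 13.4 does not end pregnancy follow-up at Visit 4, and the Trust procedure it cites, which is not available here, may add more. The expected number is tiny, and its upper end combines three worst cases.

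Much of this stands. The on-treatment reading is tenable, though the reference to the whole trial and the 28-day spacing of Visit 4 favour the wider one. The number is small. What does not follow is that the gap is closed: Section 13.7 operates only once a pregnancy is known, and the visible text attaches no action to the menses answer.

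Two smaller points are fair:
- Supply is 3 × 28 = 84 tablets, so with perfect daily dosing the last dose is Day 84 and the upper interval after a Day 78 test is 6 days, not 7. The high figure becomes 30 × (24/365) × 0.20 × 0.30 = 0.118. A missed dose can still take the last tablet to Day 85.
- Required contraception ends 14 days after UA, so Visit 4 falls 24 − 14 = 10 to 39 − 14 = 25 days after that. A positive result could be a conception after exposure and would need dating.

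**Conclusion.** The point holds. Whether or not the mitigation text is taken to include Visit 4, the protocol schedules no pregnancy test that could detect a conception in the last 10-25 days of UA exposure, and safety follow-up then closes without one. The absolute risk is low: about 0.002 to 0.12 expected pregnancies across 30 women, resting on the assumed detection lag and contraceptive failure rate and on the ovulating share implied by Section 5.4.1. It bears on safety ascertainment alone. A change is still worthwhile because the foetal risk is stated to be unknown, Section 11.1 expects no physical benefit for participants, and the remedy is very cheap. It should be made, but it is not critical to the trial's conclusions.

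**What to change.** Add a urine pregnancy test to the Visit 4 list in Section 7.1, and mark the week 17 cell of the urine pregnancy test row in Appendix 5. The mitigation statement in Section 11.2 is then true on either reading, and a positive result starts reporting and follow-up under Section 13.7 before safety follow-up ends. State that a positive result is to be dated against the last dose, since contraception is no longer required by then.

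Simply limiting the Section 11.2 sentence to on-treatment visits would settle the wording but leave the gap.

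The cost is about 30 urine dipstick tests at most, at a visit already attended, plus one line in Section 7.1 and one mark in Appendix 5. Section 7.1 provides for participants who have already completed the study, so the gain is confined to women who have yet to reach Visit 4.

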## **12 Forms and procedures for collecting data**

### **12.1 Case report forms**

Data will be abstracted from the family history medical records onto case report forms and entered into a trial specific database. Access to the ongoing trial data will be restricted to the trial team and R&D.

Data will be transcribed into an Excel spreadsheet and data verification will be performed including a quality control check of 10% of the data added into the statistical and analytical software prior to analysis as described in appendix 2.

Access to the final dataset will be restricted to the trial team and R&D. Source data for the trial will be: defined in the source data log. Source data verification will be performed as part of the monitoring for the trial and will be described in the monitoring plan.

All patients require the CRF to be completed within 1 month of entry into the study. Research staff must ensure that all source data and trial related documentation are accurate, complete, maintained and accessible for monitoring and audit purposes.

Original consent forms must be dated and signed by both patient and investigator and will be kept together in a central log together with a copy of the specific patient information sheet(s) given at the time of consent

Copies of CRFs will be retained for 15 years to comply with international regulations

### **12.2 Data flow**

Records of numbers of patients approached, assessed for eligibility, registered and lost to follow-up will be recorded as per CONSORT guidelines.

CRFs will be developed with the CI, trial management team, statistician and data manager to ensure that the data management system supports both the research aims of the study and regulatory requirements. Any CRF input amendments must be signed and dated by study staff. The data management system will be fully validated, including the provision of test data and supporting documentation. The system will be backed-up offsite every 24 hours.

Each participant will be assigned a trial identity code number, allocated for use on CRFs, other trial documents and the electronic database. The documents and database will use centre initials date of birth (dd/mm/yy) and patient number.

CRFs will be treated as confidential documents and held securely in accordance with regulations. The investigator will make a separate confidential record of the participant's name, date of birth, local hospital number or NHS number, and Participant Trial Number (the Trial Recruitment Log), to permit identification of all participants enrolled in the trial in accordance with regulatory requirements and for follow-up as required.

Completion of CRFs shall be restricted to those personnel approved by the Chief or local Principal Investigator and recorded on the 'Trial Delegation Log'.

All paper forms shall be filled in using black ballpoint pen. Errors shall be crossed out (but not obliterated by using correction fluid) and the correction inserted, initialled and dated. Corrections should be made legibly and initialled and dated by approved personnel. The reasons for significant changes must be provided.

If any data are not available, omissions should be indicated on the case report forms. The NHS Code of Confidentiality will be followed for this study.

Sensitive data stored on NHS or University computers will be encrypted to applicable NHS standards (AES256). The results of the study may be published in the medical literature but patient identity will not be revealed.

The trial data and documentation will be archived as per the trust Archiving SOP.

### **12.3 What to record in the participant family history medical records**

For each study visit, in the family history medical records, a detailed entry as to what has taken place must be recorded. In addition, the following must be filed in the notes:

- 1x copy of participant's Informed Consent Form
- 1x copy of applicable Participant Information Sheet
- 1x copy of GP letter
- Copy of test results
- Radiology Data collection sheets (baseline and week 12)

## **13 Safety reporting and pharmacovigilance**

The Principal Investigator is responsible for ensuring that all site staff involved in this trial are familiar with the content of this section and MFT SOP on Pharmacovigilance for Trust-Sponsored Clinical Trials of Investigational Medicinal Products (CTIMPs).

The following definitions are in accordance with the Medicines for Human Use (Clinical Trials) Regulations 2004 (SI2004/1031)(as amended) and EU Directive 2001/20/EC.

| TERM                                                                                                      | DEFINITION                                                                                                                                                                                                                                                                                                                                                                                                                                                                                                                                                                                                                                                                                                                                                                                                                                              |
|-----------------------------------------------------------------------------------------------------------|---------------------------------------------------------------------------------------------------------------------------------------------------------------------------------------------------------------------------------------------------------------------------------------------------------------------------------------------------------------------------------------------------------------------------------------------------------------------------------------------------------------------------------------------------------------------------------------------------------------------------------------------------------------------------------------------------------------------------------------------------------------------------------------------------------------------------------------------------------|
| Adverse Event (AE)                                                                                 | Any untoward medical occurrence in a subject to whom a medicinal product has been administered, including occurrences which are not necessarily caused by or related to that product.                                                                                                                                                                                                                                                                                                                                                                                                                                                                                                                                                                                                                                                            |
| Adverse Reaction (AR)                                                                              | Any untoward and unintended response in a subject to an investigational medicinal product which is related to any dose administered to that subject                                                                                                                                                                                                                                                                                                                                                                                                                                                                                                                                                                                                                                                                                              |
| Serious adverse event (SAE), serious adverse reaction (SAR) or unexpected serious adverse reaction | 
Any adverse event or adverse reaction that:
 
 
- Results in death
 
- Is life-threatening*
 
- Requires hospitalisation** or prolongation of existing hospitalisation
 
- Results in persistent or significant disability or incapacity
 
- Consists of a congenital anomaly or birth defect.
 
 
Important medical events*** may also be considered serious if they jeopardise the subject or require an intervention to prevent one of the above consequences.
 
The term life-threatening in the definition of serious refers to an event in which the patient was at risk of death at the time of the event; it does not refer to an event which hypothetically might have caused death if it were more severe.
 |
| Suspected unexpected serious adverse reaction (SUSAR)                                              | 
A serious adverse reaction, the nature and severity of which is not consistent with the information about the medicinal product in question set out:
 
 
- In the case of a product with a marketing authorisation, in the summary of product characteristics for that product.
 
- In the case of any other investigational medicinal product, in the investigator's brochure relating to the trial in question.
 
                                                                                                                                                                                                                                                                                                                                                                    |
| Reference safety information                                                                       | The information used for assessing whether an adverse reaction is expected. This is contained in either the investigator's brochure or the summary of product characteristics .                                                                                                                                                                                                                                                                                                                                                                                                                                                                                                                                                                                                                                                           |

**\*Note:** The term 'life-threatening' in the definition of serious refers to an event in which the trial participant was at risk of death at the time of the event or it is suspected that use or continued use of the product would result in the subjects death; it does not refer to an event which hypothetically might have caused death if it were more severe.

**\*\* Note:** Hospitalisation is defined as an inpatient admission, regardless of the length of stay, even if the hospitalisation is a precautionary measure for continued observation. Pre-planned hospitalisation e.g. for pre-existing conditions which have not worsened, or elective procedures, does not constitute an SAE.

**\*\*\* Note:** other events that may not result in death, are not life-threatening, or do not require hospitalisation, may be considered as an SAE when, based upon appropriate medical judgement, the event may jeopardise the participant and may require medical or surgical intervention to prevent one of the outcomes listed above.

